#### Modules of the intervention

Between 2011 and 2014 the research network *psychenet*: *Hamburg Network for Mental Health* implements different illness specific and general population oriented interventions and evaluates the resulting systemic interventions. The *psychenet* sub-project “*Healthcare Network Anorexia and Bulimia nervosa*” establishes a systemic ED-specific intervention containing the following components:The establishment of a network of health care professionals within the area of EDsThe development of an internet-based treatment guide for EDsThe presentation of informative short-films about EDs in several cinemas as well as a corresponding poster campaignA special outpatient clinic

The multidisciplinary network connects different healthcare professionals within the area of EDs. Practitioners from different settings with a medical and/or a background in clinical psychology regularly meet to exchange scientific knowledge as well as clinical experiences concerning AN treatment. The internet-based treatment guide (www.essstoerungen.psychenet.de) comprises information about EDs in general as well as treatment options and contact information of ED-specialized in- and outpatient institutions. The recommendations are based on the German S3-Guidelines for EDs [34]. The guide addresses individuals suffering from AN, relatives and healthcare professionals. In order to reach patients with a migration background as well, it is translated into English and Turkish. Components of the systemic intervention targeting the general population are the presentation of a short-film (see www.youtube.com/watch?v=6VPvCp_WWvI&index=2&list=PLF8DFEFE29B837EFC) in cinemas as well as a corresponding poster campaign. The poster-campaign comprises citations of the principal performer of the short-film with an eye-portrait and a short note about the prevalence of mental illness as well as a reference towards the main homepage (www.psychenet.de).

### Variables and instruments

The data is collected in a two-stage course of action with an antecedent questionnaire followed by a telephone interview. The questionnaire contains standardized instruments to measure ED pathology and comorbidity, as well as a set of questions concerning sociodemographic information, disorder onset and the initiation of treatment. The telephone consultation is started off with a diagnostic interview reviewing AN diagnosis by using the Structured Clinical Interview for DSM-IV SCID [35]. Then, questions regarding the onset of the disorder and the initiation of treatment follow to verify information collected from the questionnaire. The onset of the disorder is confirmed by requesting information about the beginning of weight loss, beginning of fear to gain weight, beginning of distortion of the body perception and the initial absence of the menstruation. In an exploratory part reasons for the individual DUI are explored.

#### Duration of untreated illness (DUI)

The DUI is understood as the number of months between illness onset and the initiation of an ED-specific treatment. Onset of the disease is conceptualized as the first occurrence of all symptoms of typical or atypical AN as described above.

#### Duration until first contact with healthcare system (DUC)

The duration until first contact (DUC) is conceptualized as the number of months between illness onset and the first contact with the healthcare system due to ED-related issues initiated either by the patient or the practitioner. Before starting an ED-specific treatment, patients often have several initial contacts with healthcare professionals or advice centers. The variable DUI can not take these contacts into account because it is defined as the duration until the initiation of a guideline-based treatment. The DUC is meant to improve the understanding of the processes preceding treatment initiation. The questionnaire lists different potential therapeutic settings for AN (inpatient, day-clinic, outpatient, ED-specific counselling) and assesses which of these have been consulted to get information and/or support concerning AN and, in each case, when the first contact took place.

#### ED pathology

ED pathology is measured by the BMI in combination with the German version of the *Eating Disorder Examination Questionnaire EDE*-*Q* [36]. The BMI is calculated from body weight and height. Current weight is requested in the questionnaire as well as in the telephone interview. Additionally, weights at disorder onset, at treatment initiation as well as at point of lowest weight are assessed in the telephone interview. Given the community-based character of the present study, it is not feasible to get externally validated weight measurements for all participants. Additionally, since patients with AN in in- and outpatient treatment institutions are weighted weekly, self-reported weight will be considered adequate. The *EDE*-*Q* assesses specific ED psychopathology on four subscales, which are restraint, eating concern, weight concern, and shape concern. For patients below the age of sixteen, the child version *Ch*-*EDE*-*Q*, [37,38] is used. The psychometric criteria of the *EDE*-*Q* are satisfactory. Objectivity is given and the test is very reliable with an intern consistency of α = .97 and a retest-reliability of r = .88. Validity could be confirmed as well [36].

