### Study procedures

#### Inclusion and exclusion criteria

In order to participate in the study, a signed informed consent is necessary. Patients below 16 years are required to provide additional informed consent from a parent or legal guardian. Moreover, participants need to have female sex, should be a minimum of ten years old and have a treatment diagnosis of typical or atypical (one criterion absent) AN according to the DSM-IV [33]. Furthermore participants should currently receive their first ED-specific in- or outpatient treatment or be current client of an ED-specific counselling center. Exclusion criteria are insufficient knowledge of the German language as well as substantial organic or psychological complaints preventing participation from the recruiting practitioner’s point of view.

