### Sample size/power calculation

Based on former international studies [25] with an average DUI of 19 months and an effect size of 0.4, we considered a DUI reduction of 4.8 months or 25% as clinically relevant. Thus, for a two-sided type-I error of 5% two samples with 100 participants each are needed to reach statistically significance with a power of 80%.

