### Study hypotheses

It is hypothesized that the systemic intervention of *psychenet* decreases the DUI in the post-group compared to the pre-group. As described above it is of great relevance to detect and treat individuals with AN sooner. Next to individual factors such as age [27] there are systemic aspects like sufficient information, availability and networking of different components of the health care system influencing patient flow into ED-specific care. The intervention focuses on spreading information about EDs, informing about paths to treatment, improving the networking of different healthcare professionals and extending the offer by establishing a special outpatient clinic. Therefore, it seems reasonable to assume that the systemic intervention decreases the duration until an ED-specific treatment is initiated. For the same reasons it is hypothesized that the systemic intervention decreases the DUC. Moreover, it is assumed that the systemic intervention leads to a reduced ED pathology as well as a reduced comorbidity with depression and anxiety at the beginning of treatment. It is further suspected that this effect is mediated by the DUI. An earlier intervention and a shorter duration of illness prior to treatment initiation may lead to a reduced severity of AN and a reduced comorbidity because treatment starts before a chronification can occur. Therefore, it is conceivable that the expected shorter DUI in the post-group leads to a decreased ED pathology and comorbidity at treatment initiation. Due to the lack of previous research these hypotheses will be analyzed exploratorily.

To display them at a glance, the hypotheses of the study are:The systemic intervention decreases the DUI in the post-group compared to the pre-group.The systemic intervention decreases the DUC in the post-group compared to the pre-group.The systemic intervention decreases the ED pathology at treatment initiation in the post-group compared to the pre-group via DUI.The systemic intervention decreases the comorbidity with depression and anxiety at treatment initiation in the post-group compared to the pre-group via DUI.

Figure 2 illustrates the expected impact of the systemic intervention on the primary and secondary outcome parameters.

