### Statistical analyses

In order to test the primary hypotheses regarding change vs. no change from pre to post assessment univariate multiple regression analysis with the dependent variables DUI and DUC as well as the independent variable period of assessment will be conducted. Additionally, recruitment setting will be included as random control variable whereas age and contact with the systematic intervention will be taken into account as a fixed control variable. Statistical significance will be taken two-sided p <0.05 throughout and regression coefficient with 95% confidence intervals (CI) will be used to express the uncertainty in the data.

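### BMI serves as a severity measure from age ten upwards without age standardisation, so a difference in age mix between the two samples would read as a difference in severity

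*Protocol article*

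**What the plan says.** Under ED pathology, the protocol article states that "ED pathology is measured by the BMI in combination with the German version of the" EDE-Q, and then that "The BMI is calculated from body weight and height". The same section adapts the questionnaire to age: "For patients below the age of sixteen, the child version" is used. It gives no counterpart for BMI, such as a percentile, a standard deviation score or a percent of expected BMI.

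Under Inclusion and exclusion criteria, participants "should be a minimum of ten years old". No upper age limit is stated, and all participants are female.

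The outcome enters the third hypothesis: "The systemic intervention decreases the ED pathology at treatment initiation in the post-group compared to the pre-group via DUI". The section Study hypotheses describes this part of the work as exploratory.

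The section Statistical analyses describes a regression "with the dependent variables DUI and DUC as well as the independent variable period of assessment will be conducted". For that regression, "age and contact with the systematic intervention will be taken into account as a fixed control variable". No model is described for ED pathology.

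**The concern.** One kg/m2 scale is used for children, adolescents and adults. Because normal BMI rises during growth, a value close to normal in a ten-year-old can mean severe underweight in a twenty-year-old. Raw BMI therefore mixes two things, how underweight the patient is and how old she is.

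This matters here for two reasons. First, the comparison is between two separate, non-randomised groups. The Discussion accepts that practitioners' adherence may lead to different participation rates, so the age mix could differ between periods for reasons unrelated to illness. Second, DUI is part of the patient's age: age at treatment initiation is age at onset plus DUI. If DUI falls and onset age does not change, growing patients reach treatment younger and have a lower expected BMI at the same severity. DUI would then act on raw BMI through growth as well as through illness, and these are the two paths that a mediation claim needs to keep apart.

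**Working it through.** **The plan's own figures.** The section Sample size/power calculation states that "we considered a DUI reduction of 4.8 months or 25% as clinically relevant", with an average DUI of 19 months, an effect size of 0.4, two-sided 5% error, 80% power and 100 per sample.

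- 4.8 / 19 = 25.3%, and the implied SD is 4.8 / 0.4 = 12 months.
- The normal approximation gives 99 per group for d = 0.4; the t-test version gives 99.1, rounded up to 100. Power at 100 per group is 80.7% (80.4% by t-test).

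These figures reproduce and are not in dispute. The article gives no figure for BMI, so the rest uses stated assumptions.

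**Shift in raw BMI from age alone, with onset age unchanged.**

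Shift = (DUI reduction in years) x (slope of reference BMI on age). The DUI reduction is 4.8 / 12 = 0.4 years. The slope is an assumption: 0.4-0.6 kg/m2 per year as the working range, 0.2-0.8 as the wider one.

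| Assumed slope (kg/m2 per year) | All patients growing | Half growing |
|---|---|---|
| 0 (adults) | 0 | 0 |
| 0.2 | 0.08 | 0.04 |
| 0.4 | 0.16 | 0.08 |
| 0.6 | 0.24 | 0.12 |
| 0.8 | 0.32 | 0.16 |

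With onset age unchanged, the shift makes the post-group's raw BMI lower.

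**Standardised size.** The BMI SD is assumed to be 1.5-2.5 kg/m2.

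- Working range, all growing: 0.16 / 2.5 = 0.06 to 0.24 / 1.5 = 0.16.
- Working range, half growing: 0.08 / 2.5 = 0.03 to 0.12 / 1.5 = 0.08.
- Extreme case (slope 0.8, SD 1.5, every patient growing): 0.32 / 1.5 = 0.21.
- For comparison, the standard error of a standardised difference at 100 per group is about sqrt(1/100 + 1/100) = 0.14.

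**Difference in age mix.** Shift = (change in the share of young children) x (gap in reference BMI between young children and adults). For illustration, a 10-point change and an assumed gap of 3-4 kg/m2 give 0.10 x 3 = 0.3 to 0.10 x 4 = 0.4 kg/m2 with no change in illness. The article gives no age distribution, so the 10 points are not a forecast.

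**Would the planned age covariate repair this?** It is stated for the DUI and DUC models only. If it were carried over to BMI as a linear term, it would not follow a curve that flattens in adulthood. Adjusting for age at treatment would also hold fixed a quantity that contains DUI, and so remove part of the pathway that hypothesis 3 is about.

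**The case against.** The sentence defining BMI is correct and is also the first step of any standardised score. The article describes no model for ED pathology and never says outright that raw values will be compared. The derivation could sit in a fuller plan that is not shown. This has some force: if that plan already standardises BMI for age, nothing needs changing. But the article does define the measure, and it adapts the neighbouring measure to age while leaving BMI as it is. Followed as written, it compares a scale whose meaning changes with age.

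A reader might go further and infer that hypothesis 3 is biased against the intervention, so that a sample treated earlier must look sicker. The documents do not support this as a general statement. It requires the same distribution of onset age in both samples, and these are different patients with no upper age limit. A public campaign could also bring older, long-untreated women into first treatment, which would make the post-group older. The Background itself cites longer illness duration in women of 40 and over. The direction is therefore conditional.

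The size is also modest. Under the working slopes with half the sample growing, the standardised shift is 0.03-0.08, well below the standard error of 0.14. The slopes, the SD, the growing share and the change in age mix are all assumptions. All of this stands and limits the weight of the point.

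**Conclusion.** The point holds in a limited form. As the article defines it, BMI does not measure the same severity across the ages admitted, and a difference in age mix between the two samples would show up as a difference in severity. In addition, if onset age is stable, the planned 4.8-month reduction would lower raw BMI in growing patients by 0.16-0.24 kg/m2 (assumed slope 0.4-0.6 kg/m2 per year), by about half that if half the sample is growing, and by about nothing in adults. That shift would run against hypothesis 3.

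It should not be read as a threat to the main result. It concerns one of two components of an exploratory secondary outcome; the primary DUI analysis, the EDE-Q and the sample size are unaffected. The change is worth making because the remedy is cheap and makes the measure comparable across ages.

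**What to change.** For the comparison of BMI at treatment initiation, and of current BMI, use an age- and sex-specific BMI standard deviation score or percent of median BMI for age. Name the reference population, state that adults are scored against its oldest age group, and report raw BMI descriptively.

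Extend this to onset weight or lowest weight only where age and height at that time are available. The ED pathology section lists weights at those points but does not say that height at those dates, or the date of the lowest weight, is recorded. In growing patients both are needed.

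The cost is one derived variable and a short derivation rule, since age, weight and height are already part of data collection. The downside is small: results depend to some degree on the chosen reference, which is why it should be named in advance.

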#### Comorbidity

Comorbid psychopathology is assessed by the depression module of the *Patient Health Questionnaire* (*PHQ*-*9*, [39-41]) and the *Generalized Anxiety Disorder Scale* (*GAD*-*7*, [42]). The *PHQ*-*9* is a self-assessment scale consisting of nine items. It is able to establish provisional depressive disorder diagnoses and grade depressive symptom severity [43]. There is strong evidence for the reliability of the instrument with an intern consistency of α = .89 and a retest-reliability of r = .84 [44]. The *GAD*-*7* is a self-assessment anxiety scale consisting of seven items. It has good reliability as well as criterion, construct, factorial, and procedural validity [42,45].

#### Control variables

The questionnaire includes sociodemographic and control variables, such as age, gender, marital status, educational level, migration background, housing situation and occupational activity. At post assessment, patients are asked to indicate any contact with parts of the systemic interventions from *psychenet*. In case of positive response, further questions clarify which of the ED-specific interventions were recognized and if treatment initiation is subjectively eased by these interventions.

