#### Recruitment

The recruitment is coordinated in cooperation with different ED-specific treatment settings in Hamburg and adjacent areas, i.e. inpatient wards, day clinics, outpatient departments and ED-specific counselling centers. Included institutions offer evidence-based treatment for AN based on the German S3-Guidelines for EDs [34]. A total of eleven clinics, nineteen outpatient departments and four counselling centers are asked to support the project with recruiting participants. A special network meeting is used to inform cooperating practitioners about the study’s content, procedure, and recruitment as well as to provide practitioners with study materials (e.g. written information about the course of recruitment, study design, inclusion and exclusion criteria as well as informed consent forms and questionnaires for participants). During the study, cooperating practitioners regularly receive phone calls to settle any questions and promote adherence.

Cooperating practitioners select eligible participants in line with inclusion and exclusion criteria. Participants found eligible are verbally informed about the aims and procedure of the study and are additionally provided with written material. In case of willingness to participate, participants are asked to sign the informed consent. Practitioners then hand out the questionnaire set, which is described later in this paper. All cooperating practitioners are required to return the completed questionnaires as well as the signed informed consents to the research team. Once all documents are complete, participants are contacted for a structured telephone interview.

The procedure will be identical in the post-survey. Participants who participated in the pre-survey are excluded from participation in the post-survey. Between the two points of data collection the systemic intervention takes place.

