### Primary outcome

The primary outcome is the DUI, defined as the time in months between the onset of AN and first specific treatment.

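### In the post wave, campaign-contact questions appear to come before the interview that settles the DUI dates, an avoidable risk of differential reporting

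*Protocol article*

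**What the plan says.** - **Primary outcome.** "The primary outcome is the DUI, defined as the time in months between the onset of AN and first specific treatment". The section on DUI gives the same definition, and one definition serves both waves.
- **Order of data collection** (Variables and instruments). "The data is collected in a two-stage course of action with an antecedent questionnaire followed by a telephone interview". Besides the standardized scales, the questionnaire has content described "as well as a set of questions concerning sociodemographic information, disorder onset and the initiation of treatment". In the interview, "questions regarding the onset of the disorder and the initiation of treatment follow to verify information collected from the questionnaire". Onset is confirmed there through four markers: the start of weight loss, of fear of gaining weight and of disturbed body perception, and the first missed menstruation.
- **Post-only items** (Control variables). The paragraph begins "The questionnaire includes sociodemographic and control variables" and goes on: "At post assessment, patients are asked to indicate any contact with parts of the systemic interventions". Patients who answer yes are asked which components they noticed and "if treatment initiation is subjectively eased by these interventions".
- **Sameness of the waves** (Recruitment). "The procedure will be identical in the post-survey". The same section has eligible patients informed of the study's aims before they consent and receive the questionnaire.
- **Analysis** (Statistical analyses). DUI is regressed on period of assessment. Contact with the intervention is one of the control variables.
- **Acknowledged limits** (Discussion). Randomization was not feasible, the DUI measure had to be newly developed, and the data are mainly retrospective. The interview review is the stated protection against distortion.

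**The concern.** The primary comparison is between two groups of patients who date, from memory, when all symptoms were first present and when specific treatment began. Any feature of the survey that prompts one group and not the other can move those dates in that group alone. A question about whether a campaign reached the patient, followed by one about whether it made starting treatment easier, invites her to reconsider the very interval being measured. If this happens before the dates are checked, the protocol's own protection, the interview review, operates after the prompt in the post wave and without it in the pre wave.

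A shift confined to the post wave goes straight into the period coefficient. With no concurrent comparison group, nothing in the design would reveal it. Shorter reported durations would look like benefit, and longer ones would hide it.

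**Working it through.** **1. Where do the post-only items sit?** The contact sentence itself names no instrument. Two statements place it:
- the Control variables paragraph says that the questionnaire carries the control variables;
- Statistical analyses lists contact with the intervention as a control variable.

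Together these put the contact items in the questionnaire, which comes before the interview. This is an inference, but the natural one. The perceived-ease item follows the contact item, and only for patients who report contact.

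**2. What is settled before and after them?** Onset and treatment start are first reported in the same questionnaire, and the article does not give the item order. The first report may therefore come before or after the contact items. The interview verification comes after them in either case.

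**3. The plan's own figures.** From Sample size/power calculation: difference 4.8 months, effect size 0.4, two-sided 5%, 80% power, 100 per wave.
- Implied SD = 4.8 / 0.4 = 12 months.
- n per wave = 2 × (1.960 + 0.842)² × (12 / 4.8)² = 2 × 7.85 × 6.25 = 98.1, so 99 by the normal approximation. The t-test version gives 99.1, rounded up to 100.
- Power with 100 per wave is 0.807 (normal) or 0.804 (t-test).

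The stated 100 is reproduced and is not in dispute.

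**4. Illustration: no true effect, mean post-wave shift of b months.** SE = 12 × √(2/100) = 1.70 months. The two-sided rejection rate is Φ(b/SE − 1.96) + Φ(−b/SE − 1.96).

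| Assumed mean shift b (months) | b/SE | Rejection rate |
|---|---|---|
| 0 | 0 | 5.0% |
| 0.5 | 0.29 | 6.0% |
| 1 | 0.59 | 9.1% |
| 2 | 1.18 | 21.8% |
| 3 | 1.77 | 42.4% |

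The t-test gives 9.0% and 21.6% at 1 and 2 months. One month is 1 / 4.8 = 21% of the target difference.

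**5. The opposite direction.** If the true reduction were 4.8 months and post reports were lengthened by 1 month on average, the expected difference would be 3.8 months. Power would be Φ(3.8/1.70 − 1.96) = Φ(0.28), about 61% instead of 81%.

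**6. Dilution.** If only a fraction f of post patients is affected, a mean shift of 1 month needs 1/f months in each of them: 2 months at f = 0.5, 5 months at f = 0.2.

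The documents give no value for b or f. Steps 4 to 6 show what a shift would do, not that one occurs.

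**The case against.** Several counter-arguments have force.

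- **Both waves hear the aims.** A reader might infer that only post patients learn what the study hopes to show. Recruitment rules that out: eligible patients are told the aims before the questionnaire, and the post procedure is the same. What differs is only the campaign-specific prompt. This stands.
- **DUI has one definition, and no difference in the date questions is described.** A reader might infer that the primary outcome is measured differently in the two waves. The text does not support that. This stands too. The statement that the procedure is identical closes the Recruitment section, and patients surveyed before a campaign cannot usefully be asked about it, so part of the asymmetry is unavoidable.
- **The mechanism is uncertain.** The perceived-ease item reaches only patients who already noticed the campaign. Treatment start is recent for patients in their first specific treatment, and onset is anchored on four separate markers. This limits how large a shift is plausible and leaves its direction open. It does not exclude one.
- **Item order is detail that an article may leave to the full protocol.** This is true of the order within the questionnaire. The order of questionnaire and interview, however, is stated, and so is the instrument that carries the control variables. The point rests on that described sequence.
- **Recall distortion is already acknowledged.** It is, in general terms. The Discussion does not mention this prompt, and the safeguard it offers appears to come after the prompt.

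**Conclusion.** The concern holds as an avoidable risk of differential reporting between the waves. On the natural reading, the post wave alone answers campaign-contact items before the interview that verifies treatment start and confirms onset. The outcome is recalled, the measure is new, and the period effect has no concurrent control.

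The size and direction of any shift are unknown. The rates of about 9% for a 1-month and 22% for a 2-month mean shift assume SD 12 months, 100 complete patients per wave, no true effect and a simple unadjusted comparison. They are illustration, not an estimate of bias. The conclusion also rests on the inference that the contact items are in the questionnaire. If they already come last in the interview, the article should say so and the point falls away.

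**What to change.** Ask the contact and perceived-ease items at the end of the post-wave telephone interview, after onset, first-contact and treatment dates have been recorded and locked. Keep everything before that point identical to the pre-survey. Contact remains available as the control variable that the regression needs, and the interviewer does not have the patient's campaign answers while checking the dates.

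The cost is a re-ordering of the post-survey material, with no new data. There is one small downside: contact would be missing for patients who do not complete the interview. Handling of missing values already counts them as withdrawals, outside the main completer analysis, but the sensitivity analysis with imputed data would have to impute contact for them as well.

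If the post-survey material can no longer be changed, report the order used and name this prompt as a limitation. The change from questionnaire to interview dates could also be compared between the waves. That check is only partial, because the questionnaire dates may themselves follow the prompt.

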## Methods

### Study design

For the study purpose, a pre-post between-subject design was chosen. DUI, duration until first contact (DUC), current ED pathology and comorbidity are measured before and after the implementation of the systemic intervention. The pre-data collection takes place between November 2012 and May 2013. Twelve months are planned for the systemic intervention. The post-data collection takes place between May 2014 and November 2014. Figure 1 illustrates the course of the data collection.

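### The contact item has no stated time limit and, for components sought because of illness, depends on the DUI itself, so entering it in the DUI/DUC regression can bias the period coefficient towards a false benefit

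*Protocol article*

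**What the plan says.** Under Control variables, the exposure item is put to the post-group only: "At post assessment, patients are asked to indicate any contact with parts of the systemic interventions from" psychenet. After a positive answer, "further questions clarify which of the ED-specific interventions were recognized and if treatment initiation is subjectively eased by these interventions". No date of contact is mentioned. By contrast, the section on the DUC says that the questionnaire records when the first contact with each care setting took place.

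Under Inclusion and exclusion criteria, respondents are already in care: "Furthermore participants should currently receive their first ED-specific in- or outpatient treatment or be current client of an ED-specific counselling center". No maximum time since the start of treatment is given. The primary outcome, DUI, is "defined as the time in months between the onset of AN and first specific treatment", so it is complete before the contact item is answered.

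Under Statistical analyses, the regression of DUI and DUC on period of assessment also includes the item: "age and contact with the systematic intervention will be taken into account as a fixed control variable".

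**The concern.** Two separate features of the item matter.

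First, contact can shorten the DUI only if it happens before treatment starts. As described, the item also counts a patient who first opened the treatment guide while in treatment, so recognised pre-treatment contact is overstated.

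Second, some components are sought because a person is ill. For the web guide and the special outpatient clinic, more untreated months during the campaign mean more opportunity for contact. Contact is then partly a consequence of a long DUI.

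The covariate role turns this into a problem for the main result. The item is asked only at post assessment. If pre-group patients are coded as not contacted, which is the natural coding but is not stated, the contact coefficient becomes contacted minus non-contacted patients within the post-group, and the period coefficient becomes non-contacted post patients minus the pre-group. The first would suggest that contact lengthens the DUI. The second would suggest that the later period shortened it. Both could appear with no intervention effect at all.

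**Working it through.** **Inputs from the protocol article.** Mean DUI 19 months, relevant difference 4.8 months, effect size 0.4, two-sided 5%, power 80%, 100 per group (Sample size/power calculation). On length, "Twelve months are planned for the systemic intervention"; the pre-survey ends in May 2013 and the post-survey runs from May to November 2014 (Study design). With a launch around May 2013, the post-survey falls about 12-18 months after launch.

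**The plan's own figure.** The implied SD is 4.8/0.4 = 12 months, and 4.8/19 = 25.3%. For a standardised difference of 0.4, the normal approximation gives 99 per group and the noncentral t gives 100 (power 0.804). The stated 100 is reproduced, so mean 19 and SD 12 are used below.

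**Assumptions not in the documents.** No intervention effect; gamma or lognormal DUI; a constant contact rate r of 2%, 5% or 10% per month; three months in treatment before the survey. Age and recruitment setting are left out.

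**Step 1: why contact can depend on the DUI.** For a component sought because of illness, opportunity = min(DUI, months from launch to treatment start), and P(contact) = 1 - exp(-r x opportunity). At r = 0.05, two untreated months give 1 - exp(-0.10) = 0.095, and fifteen give 1 - exp(-0.75) = 0.528.

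**Step 2: size of the gap.** Contacted minus non-contacted DUI in months, simulated with no effect:

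| Setting | r = 0.02 | r = 0.05 | r = 0.10 |
|---|---|---|---|
| Pre-treatment contact, treatment start at months 12-18, gamma | 3.0 | 3.7 | 5.2 |
| Same, lognormal | 2.2 | 2.7 | 3.7 |
| Share of reported contacts made only in treatment, gamma | 17% | 15% | 11% |
| Same, lognormal | 17% | 14% | 10% |

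These rows put the survey at months 15-21. With the survey at months 12-18, as the timetable implies, and the item as written (in-treatment contact counted), the gamma gap is 1.7 to 3.0 months and the in-treatment-only share is 13-20%. A lognormal DUI makes the gap smaller again.

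The gap depends on how contact arises. If contact is population-wide and accrues from launch to survey whether or not a patient is ill, every patient has the same calendar window and the gap is 0. A separate run used monthly rates of 0.03, 0.1 and 0.2 and either no lag or 0-6 months in treatment. It gave +1.9 to +9.4 months for illness-driven contact, and +0.9 to +3.9 when contact before onset and in treatment accrues at half the rate.

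**Step 3: effect on the period coefficient.** Let p be the share contacted, m1 and m0 the mean DUI of contacted and non-contacted post patients. With no effect, the pre-group mean equals p x m1 + (1 - p) x m0, so

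period coefficient = m0 - [p x m1 + (1 - p) x m0] = -p x (m1 - m0).

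Check against one simulated case (rate 0.1, no lag, campaign ending at month 12): p = 0.58, m1 = 21.5, m0 = 15.5, so -0.58 x 6.0 = -3.5, the simulated bias. Across the gamma settings of Step 2 the bias is -0.7, -1.7 and -3.5 months with treatment start at months 12-18, and -0.4 to -2.2 with the survey at months 12-18. In the separate run, illness-driven contact gave false significance in favour of the intervention in about 4-7% of runs at rate 0.03, 14-39% at 0.1 and 22-77% at 0.2, against a nominal 2.5%. With population-wide contact the bias was about 0.

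**Step 4: does dating the item cure this?** No. At rate 0.1 with the campaign ending at month 12, the bias is -3.5 with either item when there is no lag, and -2.2 (pre-treatment contact only) against -2.4 (open item) with a lag of 0-6 months. In-treatment contact that is unrelated to the DUI dilutes the contacted group but leaves the DUI distribution of the non-contacted group, which sets the period coefficient, essentially unchanged.

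**The case against.** The strongest reply is that the article plans no measure of reach and no hypothesis comparing contacted with non-contacted patients; the planned contrast is post against pre. That is true, and nothing here should be read as a flaw in a reach outcome. It does not remove the point, because contact is a planned covariate and its coefficient is that comparison.

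A reader might infer that contact marks a long DUI for every component. The article does not support this. The film and posters address the general population, so a patient could have seen them before falling ill, and the gap is then about zero.

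A reader might also infer that total reach is overstated. That is not established either. The Discussion assumes that some parts of the intervention act unconsciously, which pushes self-reported contact down, so the net direction is unknown. Only recognised contact before treatment is overstated.

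Nor does the article show that recruiting institutions expose patients to the intervention: "A special network meeting is used to inform cooperating practitioners about the study’s content, procedure, and recruitment" concerns the study, not the handing out of the guide.

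Finally, the full questionnaire is not shown and may limit the period, and the follow-up on whether treatment initiation was eased does look back before treatment. That stands as a caveat. The item as described still has no limit, and a limit would not repair the covariate problem.

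**Conclusion.** The point holds in this form. As described, the item counts contact that came too late to affect the DUI: about 10-20% of reported contacts, assuming three months in treatment and 2-10% contact per month. For components sought because of illness, contacted patients can show a DUI about 2-5 months longer with no effect, against a target of 4.8 months. The lower part of that range fits the study calendar better, and the figure is about zero for cinema and posters if exposure does not depend on illness. With contact as a covariate and the pre-group coded as not contacted, the period coefficient is then biased towards a false benefit, by about 0.4 to 3.5 months in the gamma settings at these rates. The contact rates, the time in treatment, the DUI distribution and the pre-group coding are assumptions. The direction rests only on contact becoming likelier with untreated time. The comparison of periods without contact in the model is not affected.

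**What to change.** 1. In the post-questionnaire, ask month and year of first contact with each component, as is already done for care settings.
2. Count a patient as contacted only if that month precedes the start of treatment, and state how a first contact in the same month is classified.
3. Report the share descriptively, by component, as recognised pre-treatment contact.
4. State that a difference in DUI or DUC between contacted and non-contacted patients is not an estimate of the intervention effect, and why.
5. Make the period comparison without contact as a covariate the primary analysis, keeping age and recruitment setting as planned. This step removes the bias; steps 1 to 3 alone do not.

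The cost is one date field per component, some extra recall burden, and one changed sentence in the analysis section. If contact dates are not collected, late contacts cannot be separated out at analysis.
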